#### Secondary Outcome Measures

Two-sample generalization McNemar’s test will be done to assess whether a significant change occurred between the pre- and the post-intervention assessments for dichotomous variables such as: intention to know self and partners HIV status, intention to reduce multiple sexual partners, and intention to use a condom the next time a participant has sexual intercourse. Each of these, outcomes will be assessed separately (individually). In order to judge the change, we will calculate the proportions of the dichotomous variable pre- and post-intervention in both groups. After that, we will obtain the pre- and post-intervention difference percentage at a *P* value within group and a *P* value in the intervention versus waitlist control group. This technique is documented by Katz [26]. Additionally, we will conduct a subgroup analysis of those with low-risk perception who report no condom use at last sexual encounter. This subgroup analysis will give us a more nuanced insight of the effect of the intervention to the most as risk subgroup in our study.

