## Methods

### Study Design and Hypotheses

The Swaziland Serious Games–Based HIV Prevention Trial (SGprev trial) will be a 4-week, two-arm randomized intervention trial. Participants will be randomized into 2 groups (the intervention group and a wait-list control group) in a 1:1 allocation ratio (Figure 1) [18]. The intervention will be downloadable from our website, on the Google Play store, and in popular cellular shops around Swaziland. These cellular shops already serve as distribution sites for other mobile software and apps, such as antiviruses, Opera mini, and WhatsApp, and are thus very popular in Swaziland. Additionally, the game will also be available from kiosks in all tertiary institutions in the country. Downloading the game will not be synonymous with enrolling in the trial. After downloading the game, potential participants will be redirected or prompted to visit our website where information about the trial and eligibility screening will be provided.

We plan to test whether a serious game intervention delivered on mobile phones to increase HIV risk perception, increases the intention to reduce multiple sexual partnerships, intention to know own HIV status, and intention to know all sexual partners’ HIV status will be more effective compared with current prevention efforts. Therefore, our hypotheses are that

1. The change in HIV risk perception between pre- and post-intervention assessment is greater in the intervention group compared with the change in the control group.

2. The change in HIV risk perception between pre- and post-intervention assessment will be greater among those reporting high HIV risk behavior in the intervention group compared with the control group.

3. The change in intention to have an HIV test between pre- and post-intervention assessment will be greater in the intervention group compared with the change in the control group.

4. The change in intention to reduce multiple concurrent partnerships between pre- and post-intervention assessment will be greater in the intervention group compared with the change in the control group.

5. The intervention group will report higher rate of condom use in the last sexual encounter compared with the control group.

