### Sample Size Calculation

The trial will be powered on the primary outcome measure and based on comparison of the change in HIV risk perception score from pre- to post-intervention assessment in the intervention group at 4 weeks. A study conducted in Uganda estimated mean HIV risk perception of M=3.27, SD *=* 1.03, therefore, we used this estimation as our baseline mean and SD to calculate our effect size [21]. Assuming a moderate effect size of 0.477 (identified by Chu et al [22]), alpha (two-tailed)=0.05, beta=0.20, with 1:1 allocation ratio between both groups, and a SD of the outcome in the population of 1.03, the total sample required to sufficiently power the study would be 146 (73 for each group). Moreover, assuming a 30% loss to follow-up rate [15], we then inflated the sample by 30% to yield a sample of 190. After that, we considered gender differences and once more inflated the sample by a factor of 2 to give a final sample size of 380. Finally, to ensure a balance between males and females in both groups we will recruit 190 females and 190 males. The sample size was calculated using Web-based sample size calculation software [23,24].

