#### Primary Outcome Measure: HIV Risk Perception Score

First, we will use bivariate analysis to calculate the mean between baselines and follow-up. Next, to estimate the difference between the 2 groups, we will calculate the difference between the mean change of the intervention group and the mean change of the wait-list control group using two-sample paired *t* test. We will not perform interim analysis.

Secondly, in the case that, even after randomization, we observe some baseline differences, we will use multiple linear regression to adjust for those differences; where the outcome will be the follow-up score and the independent variables will be the intervention group, baseline scores, age, gender, marital status, level of education employment status, current monthly income, and number of times players played SwaziYolo. We will present our results in standardized regression coefficients for the intervention effect on the outcome variable as previously done for this type of hypothesis [25].

Although great effort will be put to minimize attrition, it is common for eHealth trials to typically have substantial attrition [26]. For this reason, our primary outcome analysis will prioritize analysis of the subjects who adhered to their group assignment and were sufficiently exposed to the intervention. Therefore, both pre-protocol analysis (as treated analysis) as well as intention to treat analysis will be done and both results will be reported. The approach of conducting both “intention to treat analysis” together with “as treated analysis” has been observed in literature for example, Weinstein and colleagues [33] followed this approach in their randomized trial comparing surgical versus nonoperative treatment for lumbar disk herniation.

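### The binary intention outcomes are tested on pre-post change; adjusting the 4-week response for baseline is at least as precise and needs no new data

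*Protocol article*

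**What the plan says.** Under Secondary Outcome Measures in the analysis section, the dichotomous outcomes named are intention to know one's own and partners' HIV status, intention to reduce multiple partners, and intention to use a condom. The list is given as examples. A two-sample generalisation of McNemar's test is to be used "to assess whether a significant change occurred between the pre- and the post-intervention assessments for dichotomous variables". The plan will then obtain the "pre- and post-intervention difference percentage at a *P* value within group and a *P* value in the intervention versus waitlist control group". No baseline-adjusted model is given for these outcomes.

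Study Design and Hypotheses words hypotheses 3 and 4 as change. Hypothesis 3, for example, reads: "The change in intention to have an HIV test between pre- and post-intervention assessment will be greater in the intervention group". Hypothesis 5 is worded as a rate: "The intervention group will report higher rate of condom use in the last sexual encounter compared with the control group".

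A regression "where the outcome will be the follow-up score and the independent variables will be the intervention group, baseline scores, age, gender, marital status" appears only for the primary HIV risk perception score. It is conditional on baseline differences being observed, and the first analysis stated for that score is itself a comparison of mean changes.

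Table 1 schedules the intention items at both baseline and 4 weeks.

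**The concern.** A comparison of change subtracts the whole baseline response from the follow-up response. If the two are only weakly related, this adds the baseline noise to the contrast instead of removing variation. Regression on baseline subtracts only as much of the baseline as predicts follow-up.

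The stake is the chance of detecting a real effect on the intention outcomes, including those behind hypotheses 3 and 4. The trial is sized on the primary score alone, and no power is given for the binary outcomes, so nothing in the document shows that there is precision to spare. An avoidable loss makes a real effect on intentions more likely to be reported as null.

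**Working it through.** **Inputs from the protocol article (Sample Size Calculation).** Final sample 380, allocated 1:1, so 190 per arm; loss to follow-up 30%. Completers per arm: 190 × 0.70 = 133. Two-sided alpha 0.05. The article states no power or precision for the binary secondary outcomes, so there is no figure of its own to reproduce on this point.

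**Inputs that must be assumed.** The correlation ρ between the baseline and 4-week binary responses, and the prevalences at each visit.

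**Formulae.** Let s0² = p0(1−p0) and s1² = p1(1−p1) be the variances at baseline and 4 weeks. Per participant, on the risk-difference scale:

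- Var(change) = s0² + s1² − 2ρ·s0·s1
- Var(baseline-adjusted) = s1²(1 − ρ²)
- Difference = s0² − 2ρ·s0·s1 + ρ²·s1² = (s0 − ρ·s1)², which is never negative

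So in large samples change cannot beat adjustment, whatever ρ and the prevalences are.

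**Equal prevalences (s0 = s1 = s).** Var(change) = 2s²(1−ρ) and Var(adjusted) = s²(1−ρ)(1+ρ). The ratio adjusted/change is (1+ρ)/2, and the share of precision lost is (1−ρ)/2:

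| ρ | 0.2 | 0.3 | 0.5 | 0.7 | 0.9 |
|---|---|---|---|---|---|
| lost | 40% | 35% | 25% | 15% | 5% |

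An analysis that ignores baseline has variance s². Since 2s²(1−ρ) exceeds s² when ρ < 0.5, the change analysis is then less precise even than ignoring baseline.

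**Unequal prevalences.** Loss = 1 − Var(adjusted)/Var(change):

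| baseline → 4 weeks | ρ = 0.2 | ρ = 0.5 |
|---|---|---|
| 10% → 30% | 18% | 3% |
| 30% → 50% | 35% | 19% |
| 50% → 70% | 45% | 32% |
| 70% → 85% | 55% | 45% |
| 80% → 90% | 57% | 48% |

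(ρ = 0.7 is not attainable for these pairs of prevalences.)

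**Illustrative power.** Assume 133 completers per arm, 50% at baseline, and 50% v 65% at 4 weeks. By hand for ρ = 0.2, with s1 = √(0.65 × 0.35) = 0.477 in the intervention arm:

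- Change: variances 0.25 + 0.2275 − 0.4 × 0.5 × 0.477 = 0.382 and 0.25 + 0.25 − 0.4 × 0.25 = 0.400. SE = √(0.782/133) = 0.0767; 0.15/0.0767 = 1.96; power about 50%.
- Adjusted: (0.2275 + 0.25) × 0.96 = 0.458. SE = √(0.458/133) = 0.0587; 0.15/0.0587 = 2.55; power about 72%.

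Two simulations agree. One used 20,000 trials per scenario and a Mantel-Haenszel test stratified by baseline. The other used 3,000 trials and linear regression on arm and baseline with robust standard errors.

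| ρ | change v adjusted, first | change v adjusted, second |
|---|---|---|
| 0.2 | 50% v 71% | 49% v 72% |
| 0.3 | 56% v 74% | 56% v 75% |
| 0.5 | 70% v 82% | 71% v 83% |
| 0.7 | 90% v 94% | 91% v 94% |

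With no true effect, both methods rejected in about 5% to 6% of trials at 133 per arm. Neither simulation included gender.

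**The case against.** The best defence is that nothing here is wrong. The test compares the arms, holds its type I error, and matches hypotheses 3 and 4, which are worded as change. The primary score is also first compared by change, so the plan is consistent, and no power was promised for secondary outcomes. All of that stands. It does not remove the inefficiency: under randomisation the difference in change and the baseline-adjusted risk difference estimate the same effect, so adjusting leaves the hypotheses intact.

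Several stronger readings do not hold:

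- A reader might infer a fixed loss, such as 15% to 40%. That range needs ρ between 0.2 and 0.7 and similar prevalences at both visits, and the article gives neither.
- A reader might infer that the plan already adjusts the primary score for baseline and so treats its secondary outcomes inconsistently. The regression for the primary score is a conditional second step.
- A reader might extend the point to hypothesis 5. That hypothesis is framed as a rate, and the analysis section names intention to use a condom, not use at last sex. Because its list is open, the test for hypothesis 5 is unclear.

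A further objection is that Baseline Data Collection places the baseline questionnaire after randomisation, and Randomization says participants are not blinded. Baseline answers could therefore reflect allocation. This stands, but it counts against both analyses. A baseline shift enters the change score with weight 1 and the adjusted estimate with the regression slope, which for a binary response is a difference of two probabilities and cannot exceed 1.

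**Conclusion.** The point holds as lost efficiency on the binary intention outcomes, including those behind hypotheses 3 and 4. It is not bias, it leaves the sample size of 380 untouched, and it contradicts no stated power. The direction is certain in large samples. The size depends on assumptions: 5% to 40% for ρ from 0.9 down to 0.2 with equal prevalences, and about 3% to 57% across the unequal-prevalence scenarios computed. In the illustrative scenario the practical gain is large at ρ = 0.2 (about 50% to 71% power) and small at ρ = 0.7 (90% to 94%). It is a worthwhile, inexpensive improvement, not a correction of an error.

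**What to change.** For each dichotomous secondary outcome, make the between-arm test a regression of the 4-week response on arm and baseline response, with gender added because men and women are recruited to quota. Fit it whether or not baseline differences are seen. Report the adjusted risk difference with its 95% CI, which stays on the percentage-difference scale the plan already uses; an odds ratio would not. Linear regression with robust standard errors is the form checked above, without gender. Keep the pre and post proportions and within-group changes as description only. State whether condom use at last sex (hypothesis 5) is analysed in the same way.

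Have the baseline questionnaire completed before allocation, since both the adjustment and any change analysis rely on a baseline that allocation cannot influence.

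The analysis change costs only wording and needs no new data or participants. The baseline change reorders two steps in the web-based enrolment, and the trial is still at the pre-initiation stage.

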### Informed Consent

All participants will be required to give Web-based informed consent (Multimedia Appendix 3) before participation in the study. An online forum via Facebook and WhatsApp will be setup to allow participants to ask questions related to this research. They will be informed about the purpose of the study, its strict confidentiality, importance, and voluntary nature of their participation, their right to end the participation at any time without having to state a reason. Lastly, participants will be informed that the aggregated results (not individual case data) will be disseminated to improve the intervention package and general HIV prevention in Swaziland (see SGprev Trial information sheet in Multimedia Appendix 4).

### Protection of Personal Information

The following measures will be taken to protect participant’s personal information:

1. Permission will be sought from study participants to collect game usage data (login data) automatically.

2. All participants’ data will be stored under encrypted servers to protect participants’ information.

3. Participants’ cellphone numbers will be stored in a password protected file and will not be used for purposes other than those outlined in this protocol. After the trial, all cellphone numbers will be deleted.

### Expected Adverse Effects and Countermeasures

During or after the study, participants may develop psychological distress or embarrassment. All efforts to prevent this psychological distress or embarrassment will be put in place. If despite our efforts any psychological issue arises during the intervention and data collection, the research team will refer the participants’ to the nearest counselor (who is well vest on psychological issues) for appropriate psychological care and support via text messaging or calling. Participants will be encouraged to self-report any feelings of distress or discomfort to the research team using Web-based tools such as the WhatsApp app, Facebook private message, or via our contact details provided in the study information sheet including a toll-free number for HIV counseling.

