### Measurement Instrument

A self-administered structured Web-based questionnaire was created based on review of both Swazi and international literature. For example, questions relating to sociodemographic characteristics were adopted from the 2007 Swaziland Demographic Health Survey, and those related to risky sexual behavior and intention to change behavior were developed from our formative studies. Additionally, the Perceived Risk of HIV Infection Scale (PRHS; found to have excellent internal consistency Cronbach alpha=0.88) [11] will be used to assess the primary outcome of this study. Past research has used a variety of approaches to measure HIV risk perception including single likelihood assessments [21,25]. The 8-item PRHS scale incorporates items assessing cognitive assessments of risk (eg, chance of infection), as well as intuitive assessments (eg, feeling vulnerable, worry, gut feeling about likelihood), and salience of risk (eg, thought about risk, can picture it happening) to provide a more comprehensive measure of perceived risk of HIV infection, thus our choice to use this scale. The questionnaire will be converted into a Web-based format accessible via a link. Detailed variables assessed by the questionnaire are described in the section below and the questionnaire is presented in Multimedia Appendix 2. The trial tools were piloted among respondents known to the principal investigator, who will not be part of the main trial, in order to assess Web-based eligibility screening functionality; user verification; participant randomization functionality; questionnaire skip logic functionality; and the average length of time it takes to complete the questionnaire.

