**User experience**			
	Would you recommend the game to your friends?		X
	How did you hear about this game?		X
	Number of times player reached the end of the game		X
	Level of satisfaction about the game		X

^a^Timing of assessment.

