#### Four-Weeks Follow-Up Data Collection

Trial participants will be followed-up for 4 weeks, the game will collect log data and send this data to our servers when the participant goes on the Internet, this will allow us to assess the exposure to the intervention without over burdening our participants to manually send us their usage data. Data captured will be limited to login data. In addition to this, a Web-based questionnaire will be sent to participants at the end of the follow-up period. Participants who will miss their 4-week follow-up assessment will be actively traced though phone calls and text messages.

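### Distress or embarrassment is expected, but the only detection route described is encouraged self-report, and no listed measure or analysis allows a reliable comparison between arms

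*Protocol article*

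**What the plan says.** Under Expected Adverse Effects and Countermeasures, the protocol article accepts that "participants may develop psychological distress or embarrassment" during or after the study. If a problem arises, "the research team will refer the participants’ to the nearest counselor". On how a problem comes to the team's notice, it says: "Participants will be encouraged to self-report any feelings of distress or discomfort to the research team using Web-based tools". The tools named are WhatsApp and Facebook private message. The contact details in the information sheet are offered as well, including a toll-free HIV counseling number.

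For scheduled data, Four-Weeks Follow-Up Data Collection states that "a Web-based questionnaire will be sent to participants at the end of the follow-up period". The game also sends usage logs, but "Data captured will be limited to login data".

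On questionnaire content, Measurement Instrument says: "Detailed variables assessed by the questionnaire are described in the section below and the questionnaire is presented in Multimedia Appendix 2". The same section describes the primary scale, the PRHS, as covering cognitive items "as well as intuitive assessments (eg, feeling vulnerable, worry, gut feeling about likelihood") and items on how salient the risk is. In Table 1, the follow-up rows closest to a participant's reaction are the user-experience rows, ending with "Level of satisfaction about the game".

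**The concern.** The article does not simply leave harms to another document. It names the harm it expects and fixes the way in which cases are found. That way is weak for this harm, because a person who is embarrassed is poorly placed to message the research team about it. The count of reports then depends on willingness to come forward as well as on how many people are affected.

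Two features of this trial add to the problem. Participants are not blinded (Randomization), so the tendency to report may differ between those who have played the game and those on the wait list. The intervention also aims to raise a score that contains worry and feeling vulnerable, and a larger rise counts as success. If some players became distressed, that could move in the same direction as the primary outcome, and no separate measure is described that would help a reader judge this.

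At stake are how fully affected participants come to the team's notice, and whether the trial report can say anything dependable about distress by arm.

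**Working it through.** The article states no distress rate and plans no harms analysis, so there is no figure to reproduce. The main check is a comparison of sections.

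**1. Detection.** Expected Adverse Effects and Countermeasures gives encouraged self-report and referral. It gives no scheduled question, instrument or time point, and does not say that reports will be recorded or counted by arm.

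**2. Listed measures.** Primary Outcome Measure gives the PRHS at baseline and 4 weeks. Table 1 gives sexual history, intentions, partner history, demographics, contact information and user experience. None of these rows asks about distress, discomfort or embarrassment. Satisfaction with the game is a different question.

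**3. Other data.** The logs hold login data only, so they cannot show distress.

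**4. Analysis.** Baseline Characteristics, Primary Outcome Measure and Secondary Outcome Measures (all under Data Management and Statistical Analysis) contain no comparison of distress.

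**5. Feasibility of a comparison.** Description of the Intervention says that wait-list controls complete the same baseline and posttest measures. An item added to the questionnaire would therefore be asked in both arms without a new visit or contact.

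**Illustration (assumed rates).** Inputs from the article are 380 participants allocated 1:1, hence 190 per arm, and 30% loss to follow-up. The 10% and 20% distress rates and the 10% to 50% reporting fractions are assumptions.

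- *Incomplete reports.* Distressed: 190 × 0.10 = 19. Heard from: 19 × 0.10 = 1.9 to 19 × 0.50 = 9.5. Not heard from: 9.5 to 17.1.
- *Unequal reporting, no true difference.* With 19 distressed in each arm, 50% reporting among players and 10% among controls gives 9.5 against 1.9 reports, an apparent fivefold excess.
- *Unequal reporting, true doubling hidden.* With 38 distressed players (20%) and 19 controls (10%), 10% and 20% reporting gives 3.8 in each arm.
- *What zero reports would show.* Let f be the unknown fraction of distressed people who report. By the rule of three, no volunteered report among 190 bounds the true rate at about 3/(190 × f). This is 3/95 = 3.2% if f = 0.5 and 3/19 = 15.8% if f = 0.1. The bound cannot be used without knowing f.
- *A solicited item.* Expected answers per arm: 190 × 0.70 = 133. No positive answer bounds the rate at 3/133 = 2.3%. This holds only for respondents and only if they answer truthfully.
- *Power.* For true rates of 10% and 20% (two-sided 5% level), power with full disclosure among 133 per arm is 0.63. With volunteered reports from 190 per arm it is 0.46, 0.21 and 0.12 when 50%, 20% and 10% of cases are reported. For 5% against 10%, the solicited item has power 0.34. The item is better than volunteered reports in these settings, but its use is estimation by arm and not a confirmatory test.

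**The case against.** The strongest objection is that the questionnaire itself is in Multimedia Appendix 2, which is not shown. Table 1 is headed as secondary outcome measures and is not a full item list: it omits the PRHS and gender, both of which the trial uses. A reader might infer that the 4-week questionnaire asks nothing about distress. The documents do not establish that. They show only that no such item is among the measures the article lists. This part of the objection stands, and the fix is worded accordingly.

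Several other tempting readings also go too far:

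- *That no comparison by arm is possible.* Volunteered reports could be counted by arm. The counts would be unreliable, but they would exist.
- *That those who stay silent receive no help.* Reporting is actively encouraged, and a toll-free counseling number is given to everyone, so a participant who never messages the team still has a route to support.
- *That only players have something to attribute distress to.* Controls answer the same questions on sexual history and HIV risk, and the adverse-effects section covers data collection as well as the game. Differential reporting is a possibility that comes with the open design, and its direction and size are unknown.
- *That a rise in the PRHS cannot be told apart from harm.* HIV-specific worry is part of the construct the scale is meant to measure, and the article nowhere equates it with distress. The overlap is an inference from the scale's content.
- *That an absence of messages would be taken as evidence of safety.* No section plans a safety conclusion of any kind.

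It is also true that nothing here contradicts another section, and that a solicited item shares some of the same weakness, since people lost to follow-up or unwilling to disclose do not show up in it either. What survives is that the article states a single, passive method of finding the harm it expects, and that a better one fits into a questionnaire both arms already receive.

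**Conclusion.** The point holds as a weakness in how harm is ascertained. It is not an error or an inconsistency. On the text available, distress or embarrassment reaches the team only through encouraged self-report, no listed measure captures it, and no comparison by arm is described. A dependable statement about distress by arm would therefore not be available, and a separate measure would help in interpreting a rise in a scale that includes worry and vulnerability.

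The size cannot be derived from the documents. The counts, bounds and power values above rest on assumed distress and reporting rates and serve only to show the mechanism. The conclusion is conditional on Appendix 2 containing no distress item. If it has one, what remains is to list it and to plan its reporting by arm. The change is worth making before recruitment, because post-intervention answers that were never asked for cannot be recovered later.

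**What to change.** State whether the Appendix 2 questionnaire contains a distress or discomfort item. If it does, add it to Table 1 and say that it will be reported by arm.

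If it does not:

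- add one or two closed distress or discomfort items to the 4-week Web questionnaire, worded identically for both arms;
- route positive answers to the referral pathway that the adverse-effects section already describes;
- report the number answering and the proportion positive by arm, with confidence intervals, as a safety outcome;
- keep the existing self-report channels alongside.

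Showing the PRHS worry and vulnerability items beside the chance-of-infection items would be informative but is optional.

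The cost is one or two questions in a questionnaire that is sent to everyone anyway, a row in Table 1, slightly longer completion, some more referrals and an ethics notification. The article gives the study's status as preinitiation, so the change can be made before any participant is enrolled.
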